##### Anthropometric measures

Participants’ heights were measured to the nearest 0.1 cm using a portable stadiometer (Shorr Productions; Olney, MD). Weights were measured to the nearest 0.1 kg using an electronic scale (Seca, Model 770; Hamburg, Germany). The average of two measurements was used for both height and weight. Body Mass Index (BMI) was calculated and expressed as kg/m^2^. For statistical analyses, BMI Z scores were created by assessing the deviation of each participant’s value from the mean values reported in the CDC growth charts (http://www.cdc.gov/growthcharts). Waist circumference was measured twice, at the level of the umbilicus, to the nearest 0.1 cm using a measurement tape.

##### Parent survey

One parent or guardian for each child completed a survey to assess demographic, family/home social and physical environment, and parental characteristics that were considered potential correlates of children’s physical activity and were consistent with the social ecological framework for the study. The survey was adapted from Sallis and colleagues [28,29]. Adults reported their children’s dates of birth, genders, and ethnicities (African American, White, Other) as well as their own relationships to participating children. Additionally, we asked for respondents’ ages (e.g., under 25, 25-34, 35-44), marital status, educational attainments as an indicator of socioeconomic status, heights, weights, and ethnic backgrounds. Adults’ BMI was calculated from parent self-reported heights and weights and expressed as kg/m^2^. Adults’ participation in physical activity was assessed with the Baecke questionnaire [30]. Family support for physical activity was calculated as the average of responses to five items each regarding frequency of (a) encouragement of physical activity for the participating children, (b) participation in physical activity with the children, (c) provision of transportation to physical activity facilities, (d) watching the children during physical activities, and (e) telling children that physical activity is good for them, responding adults and another household adults (when applicable) [28]. The responding parents also indicated the number of the participating children’s siblings living at home.

Home equipment for physical activity was assessed using a checklist of items found in homes and outdoor play areas. Responding adults reported the items that were used by the participating children and a sum of items was calculated for each child. Park distances, park usages, and park safety were assessed by asking adults to indicate the distance from their homes to the nearest park where their children could be physically active or play sports, how often the adults took their children to that park, and the parents’ perceptions of the reputation of the closest park [28]. Adults also reported their perceptions of their children’s athletic competence compared to other children of the same age and sex, number of sports teams and organized physical activity programs in which the children participated, and amount of screen time [28].

##### Data analysis

Descriptive characteristics were calculated for demographic variables and physical activity by wave and sex. For the first study aim, three mixed-model ANCOVAs, following intention-to-treat principles [23], were used to examine the effects of the SHAPES intervention on total physical activity (min/hr), moderate-to-vigorous physical activity (min/hr), sedentary behavior (min/hr), and physical activity energy expenditure (kcal/kg/min). The first model adjusted for the baseline physical activity variable and wave. The second model added demographic variables (i.e., gender, race and parent education). The third model adjusted for whether the school day was half-day (3-4 hours) or total day (6.5 to 7 hours). We used multiple imputation (data augmentation using Markov Chain Monte Carlo generation) to replace missing outcome data for the physical activity variables, height, and weight for the follow-up measure. For the second aim, a mixed-model ANCOVA was used, testing the interaction of group by factor. In all analyses, preschool was treated as a random variable with students nested in school and group (intervention versus control). Eight children with a twin or sibling included in the study were excluded from the analyses.

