## Methods

### Design

The overall design of SHAPES was a two-year randomized trial (nested cohort design), with two conditions, two measurement occasions, and preschool serving as the unit of analysis (see Table 1 for logic model for the study). Sixteen schools (eight intervention and eight control) were invited to participate and met the following eligibility criteria: the program was educative in nature and met for at least three hours per day and for 180 days per school year; the curriculum met state standards and focused on developmental and pre-academic skills for preschoolers (e.g., emergent literacy, mathematics, social development). The two major types of schools involved were public and private four-year-old pre-kindergartens and tuition-based programs, most of which were operated by religious or commercial organizations. A stratified random sample of schools meeting the described criteria was drawn and invited to participate in the study. If a preschool declined to participate, a replacement program was selected from the same stratum. Baseline and follow-up data were collected for each school year of the study. The duration of the first intervention year was approximately 15-25 weeks, and the second intervention year was approximately 31 weeks in duration. During the first year of the study, a particular group of students was assessed at baseline and follow-up. During the second year of the study, another cohort (i.e., new students in a particular teacher’s classroom) was assessed at baseline and follow-up; thus, the duration of the intervention at a given preschool was two years, but two separate cohorts were assessed in the measurement protocol (one each year). The study was approved by the University of South Carolina’s Institutional Review Board.

**Table 1 T1:** SHAPES logic model

** Inputs**		** Outputs**		** Outcomes**
**What we invest and**	**Who is reached and**	**Changes made by “change**	**Organizational changes**	**Individual behavior**
**what we do**	**expected effects**	**agents” (intervention**	**in preschool setting**	**change (activity-related**
		**implementation)**		**behaviors)**

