### Participants

Participants were children who were assigned to the 35 4-year-old classrooms in preschools that agreed to participate in the study. Approximately 13-37 children, from one to seven classrooms per preschool, were recruited and met eligibility criteria during each school year. The total sample across two years was approximately 500 children. To be eligible for the study, children’s parents must have provided informed consent and indicated that they expected their child to remain enrolled in the same preschool through the end of the current academic year. All parents of children assigned to 4-year-old classrooms in participating preschools were invited to involve their children in the study. Children were excluded from the study if they had a disability that would invalidate accelerometry as a measure of physical activity (e.g., use of wheelchair, employment of a walker) or if they were outside the 3-5 year-old age range. If there were siblings in the sample, data from only one child per family will be used for analyses.

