### Sample size

For the first study aim, sample size was calculated based on Murray’s formula for calculating detectable difference of a mixed-model ANCOVA [23]. Variance components for preschool physical activity were estimated from the research team’s prior work [14]. Detectable differences for all measures were between 0.30 and 0.43 standard deviation units (small to medium sized effects), which translated to detectable differences of 0.62 minutes of MVPA per hour, 1.63 minutes of sedentary time per hour, and 0.33 ml/kg/min of energy expenditure, assuming a conservative estimate of measuring 25 children per preschool. For the second aim, calculations were based on a mixed-model regression approach, with condition (intervention versus control) as a fixed effect and preschool nested within condition as a random effect. Because more degrees of freedom were accounted for in this analysis, the calculations for the first aim estimated a more conservative sample size than what was necessary for the second aim. Power calculations were not needed for the third aim, as this type of evaluation is predominantly descriptive in nature.

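### Follow-up outcomes are imputed by MCMC data augmentation with no stated link to preschool; if run single-level, the intervention standard error is too small

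*Protocol article*

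**What the plan says.** The Data analysis section names the method for missing follow-up data: "We used multiple imputation (data augmentation using Markov Chain Monte Carlo generation) to replace missing outcome data for the physical activity variables"; the same sentence extends it to follow-up height and weight. It does not list the variables or levels of the imputation model.

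The same section describes the models for testing: "In all analyses, preschool was treated as a random variable with students nested in school and group (intervention versus control". That sentence follows the description of the ANCOVA models. It does not mention the imputation.

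The Design section makes preschool the unit of inference ("two measurement occasions, and preschool serving as the unit of analysis") and gives the number of clusters: "Sixteen schools (eight intervention and eight control) were invited to participate".

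The Sample size section states "sample size was calculated based on Murray’s formula for calculating detectable difference of a mixed-model ANCOVA", with the result "Detectable differences for all measures were between 0.30 and 0.43 standard deviation units (small to medium sized effects", "assuming a conservative estimate of measuring 25 children per preschool". Alpha, power and the ICC are not printed. The Participants section adds: "The total sample across two years was approximately 500 children".

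**The concern.** Between-preschool variation is the error term for every aim 1 comparison, and 16 preschools leave only 14 degrees of freedom to estimate it. An imputation model should therefore carry at least the structure of the analysis model.

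MCMC data augmentation, named without qualification, usually means drawing from one multivariate-normal distribution for all children. A child imputed that way is drawn around the mean for the arm and covariates, not around the child's own preschool. The completed data then look more alike across preschools than they are, and the mixed model reads a smaller preschool variance from them. Confidence intervals for the intervention effect become too narrow and the test too liberal. The same completed data would feed all four aim 1 outcomes and all three models.

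**Working it through.** **1. The plan's own figure.** With m = 25 children per preschool, g = 8 preschools per arm, and assumed two-sided alpha 0.05, 80% power and 14 df:

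detectable difference = (t₀.₉₇₅ + t₀.₈₀) × √[2(1 + (m − 1)ICC)/(m g)] = (2.145 + 0.868) × √[2(1 + 24 ICC)/200]

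- ICC 0: 3.013 × 0.100 = 0.301 SD
- ICC 0.043: 3.013 × √(2 × 2.032/200) = 0.429 SD

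The printed range of 0.30 to 0.43 SD thus fits residual ICCs from about 0 to 0.043. Other assumptions move the upper value: normal quantiles give 0.057 at 80% power, and 90% power gives 0.022 (t) or 0.032 (normal). At 90% power, though, the smallest attainable difference is 0.349 (t) or 0.324 (normal), so 0.30 would not be reached.

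**2. Inputs for the imputation check.** 500/16 ≈ 31 children per preschool (Participants, Design). Assumed: baseline-outcome correlation 0.5, so residual variance 0.75; missing fraction f of 10-30%, completely at random; ICC 0.01, 0.043 or 0.10.

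**3. Mechanism by hand, single-level imputation.** Let b = 0.75 × ICC be the preschool variance, w = 0.75 − b the child variance, and n = 8 × 31 = 248 children per arm. A completed preschool mean keeps only (1 − f) of its own preschool effect, so b enters as (1 − f)²b: 81%, 64% or 49% of its true size at 10, 20 or 30% missing.

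- Within-imputation variance: W = (2/8)[(1 − f)²b + ((1 − f)w + 0.75f)/31]
- Between-imputation variance: B = 2 × 0.75f/n + f² × 2 × 0.75/((1 − f)n)
- True variance of the estimate: V ≈ (2/8)[b + w/((1 − f)31)]

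At ICC 0.10 and f = 0.20, b = 0.075 and w = 0.675:

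- W = 0.25 × (0.048 + 0.0223) = 0.0176
- B = 0.0012 + 0.0003 = 0.0015
- reported SE = √0.0191 = 0.138
- V = 0.25 × (0.075 + 0.0272) = 0.0256, so true SD = 0.160
- ratio = 0.86

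**4. Simulation under the null.** 20 imputations, Rubin's rules with small-sample df, a preschool-level t test on 14 df standing in for the mixed model, and 5,000 trials per cell (Monte Carlo error of type I error about 0.003).

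| ICC | Missing | Hand ratio | Simulated SE / true SD | Type I error |
|---|---|---|---|---|
| 0.01 | 10 / 20 / 30% | 0.98 / 0.97 / 0.96 | 0.99 / 0.97 / 0.95 | 0.042 / 0.041 / 0.032 |
| 0.043 | 10 / 20 / 30% | 0.95 / 0.90 / 0.87 | 0.95 / 0.91 / 0.87 | 0.057 / 0.058 / 0.059 |
| 0.10 | 10 / 20 / 30% | 0.93 / 0.86 / 0.81 | 0.92 / 0.86 / 0.80 | 0.060 / 0.069 / 0.088 |

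Smaller runs (800 to 3,000 trials per cell) put type I error at ICC 0.043 between about 5% and 8%, mostly 5-7%. A run with a REML random-intercept model in place of the t test (600 trials per cell) gave ratios of 0.90 at ICC 0.05 and 0.85 at ICC 0.10 with 20% missing, so the stand-in test does not drive the result.

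**5. Alternatives, same setting.**

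- Preschool as fixed indicators in the imputation: SE / true SD 1.00 to 1.23 over ICC 0.01-0.10, so usually too large.
- Preschool random intercept in the imputation, 20% missing (1,000 trials per cell): 1.00 at ICC 0.043 and 0.98 at ICC 0.10; type I error 0.045 and 0.050.
- Observed outcomes only: 0.98 to 1.02. The true SD is no worse than with single-level imputation (0.159 against 0.160 at ICC 0.10, 20% missing).

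**The case against.** The strongest reply is that the article nowhere says the imputation ignored preschool. Data augmentation is an algorithm; it can carry preschool indicators or a random effect, and a condensed article may leave the imputation model to the full plan. The sentence making preschool random in all analyses might even be read to cover imputation.

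Much of this stands. A reader might infer that the plan imputes with no preschool structure as a stated fact; it does not, and the single-level reading comes from the usual meaning of the named method. The point survives because the article does commit to a named method, and neither of its usual forms (without preschool, or with preschool indicators) gives reliably correct standard errors.

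A reader might also infer that imputing outcomes adds nothing over a mixed model on observed data. That is too strong:

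- Follow-up height and weight are imputed too, and both enter the energy expenditure calculation in the Accelerometry section, so a child with valid accelerometry but no weight has a partly observed outcome.
- A child may meet the school-day wear rule but not the stricter total-day rule.
- Parent survey variables could inform the imputation.

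Finally, a reader might infer inflated type I error for every aim 1 outcome. The 0.30 SD figure fits an ICC near zero, where the simulations show no inflation.

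**Conclusion.** The concern holds conditionally. If the data augmentation was single-level, the intervention SE is understated, by an amount that depends on two quantities the article does not give.

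- ICC about 0.043, 10-30% missing: SE about 5-13% low, type I error about 5-7%.
- ICC 0.01: SE 1-5% low with no type I inflation, which is negligible.
- ICC 0.10: SE about 8-20% low, type I error about 6-9%.

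An ICC of 0.20 or 35% missing would give larger effects, but these are extremes. The 0.043 value rests on alpha 0.05, 80% power, t quantiles and detectable differences expressed in residual SD units. All sizes assume data missing completely at random and a baseline correlation of 0.5. The documents do not establish that the trial's intervals are wrong. They do show a named method that, as usually run, does not match the preschool-level analysis.

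**What to change.** State and use a two-level imputation model with a preschool random intercept, and include condition, wave, the baseline value and the covariates of the analysis models. Keep the imputation of height and weight within it, because energy expenditure needs them. Report the mixed-model ANCOVA fitted by REML to the observed follow-up outcomes alongside it, or make that the main analysis. Do not rely on preschool indicators as a substitute for the random intercept. Report the missing fraction by arm and preschool and the estimated ICC, so that readers can judge how much the choice matters.

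The cost is a change of software and wording, and slightly wider intervals. No new data are needed.

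### Multiple imputation is stated for follow-up outcomes only, so missing baseline and demographic covariates fall outside it and Models 1 and 2 for Aim 1 may rest on different children

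*Protocol article*

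**What the plan says.** All references are to the protocol article.

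- **Imputation (Data analysis).** Multiple imputation by MCMC data augmentation was used "to replace missing outcome data for the physical activity variables, height, and weight for the follow-up measure". The sentence limits the scope both by variable and by time point.
- **Models (Data analysis).** "The first model adjusted for the baseline physical activity variable and wave". Model 2 adds gender, race and parent education. Model 3 adjusts for a half-day or full-day programme; whether it keeps the Model 2 covariates is not stated. The analyses are described as "following intention-to-treat principles".
- **Source of the demographics (Parent survey).** One parent or guardian per child reported the child's "dates of birth, genders, and ethnicities (African American, White, Other"), and the respondent's own education.
- **Source of the baseline values (Accelerometry).** A usable activity value needs enough wear on at least three days. Energy expenditure also needs sex, height and weight, through the resting-expenditure equation.

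No method is described for a missing baseline value or a missing demographic item.

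**The concern.** An ANCOVA fits only records whose covariates are all present, unless some method supplies the missing ones. Taken at its word, the plan treats two kinds of incomplete child unequally. A child with no follow-up accelerometry is kept, with an imputed outcome. A child with measured follow-up accelerometry but an unanswered race or education item is lost from Model 2. A child with a measured outcome but no baseline value is lost from Model 1 as well. For energy expenditure, a missing baseline height or weight has the same effect, because imputation of those two is stated for follow-up only.

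Three things are at stake. The first is some precision. The second is the comparison of Model 1 with Model 2: if the sets differ, a change in the intervention estimate mixes covariate adjustment with a change of sample. The third is the intention-to-treat description, which is hard to sustain if children with observed outcomes are left out for an incomplete questionnaire.

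**Working it through.** **1. Which covariates lie outside the stated imputation**

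| Model | Covariate | Within stated scope? | Can be missing for a child? |
|---|---|---|---|
| 1 | Baseline activity value | No | Yes (wear; also height and weight for energy expenditure) |
| 1 | Wave | Not needed | No, fixed by design |
| 2 | Gender, race, parent education | No | Yes, through unanswered survey items |
| 3 | Length of school day | Not needed | Hardly, it is a preschool characteristic |

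**2. How many distinct sets of children arise**

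Let b be the share with no baseline value and d the share with a missing demographic item, taken as independent. Neither rate is in the article; all values are assumptions. From N = 500:

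- Model 1: n = 500(1 - b)
- Model 2: n = 500(1 - b)(1 - d)

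| b | d | Model 1 | Model 2 |
|---|---|---|---|
| 0 | 0 | 500 | 500 |
| 0 | 5% | 500 | 475 |
| 0 | 10% | 500 | 450 |
| 0 | 20% | 500 | 400 |
| 5% | 10% | 475 | 428 |
| 10% | 20% | 450 | 360 |

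A missing baseline value removes the same child from Models 1 and 2. Only a missing demographic item can separate them. Model 3 matches Model 2 if it is cumulative, and Model 1 if it adds school-day length to Model 1 alone. So at most two sets arise for each outcome, and only one if d = 0.

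**3. The plan's own detectable difference**

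The Sample size section gives 0.30 to 0.43 SD at 25 children per preschool, without alpha, power or ICC. I assume two-sided 5%, 80% power, 8 preschools per arm (14 df) and no variance reduction from covariates:

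DD = (t[0.975,14] + t[0.80,14]) × sqrt(2(1 + (m - 1)ICC)/(8m)), where the t sum is 3.013.

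- m = 25, ICC 0: 3.013 × sqrt(2/200) = 0.301
- m = 25: DD = 0.43 at an ICC of about 0.043

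The stated range is attainable under these assumptions. This is not a full reproduction, since the inputs are not given.

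**4. Loss of precision**

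About 500 children in 16 preschools gives m = 31.25. Losing 10% gives m = 28.1; losing 20% gives m = 25.

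| Loss | m | DD at ICC 0.04 | DD at ICC 0 |
|---|---|---|---|
| 0 | 31.25 | 3.013 × sqrt(2 × 2.21/250) = 0.401 | 3.013 × sqrt(2/250) = 0.269 |
| 10% | 28.1 | 0.410 | 0.284 |
| 20% | 25 | 3.013 × sqrt(2 × 1.96/200) = 0.422 | 0.301 |

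If the starting point were instead 25 measured children per preschool, a loss of 10-20% would move 0.301 to 0.318-0.337, and 0.429 (ICC 0.043) to 0.441-0.454.

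**5. Movement of the estimate from the change of sample alone**

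Suppose Model 2 lost 20% at random relative to Model 1. The SD of the resulting change in the estimate is sqrt(SE_sub² - SE_full²). At ICC 0.04 this is sqrt(0.0196 - 0.01768) = 0.044 SD; at ICC 0 it is sqrt(0.010 - 0.008) = 0.045 SD. This is chance variation, not bias. It ignores the variance reduction from baseline adjustment, and it needs the whole 20% to come from demographic items.

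**The case against.** The strongest reply is that omission is inferred, not stated. The article nowhere says that children with missing covariates were dropped. MCMC data augmentation can fill covariates that are placed in the imputation model, and that model is not described. An article also commonly leaves such detail to a fuller plan. This stands in part: silence alone would be no finding. But the article is not silent. It names what was imputed and at which time point, and the covariates are not among the named variables.

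Second, the loss may be small. The Parent survey section reports that a survey was completed for each child, so what remains is unanswered items on three basic questions. Missing baseline activity arises largely through short wear, which the Accelerometry section already handles by exclusion, and that loss is common to Models 1 and 2. Both remarks are fair. They limit the size without removing the gap.

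Third, a 20% loss from 500 leaves 400 children, or 25 per preschool, which is the number the sample size already assumed. That is correct, and it keeps the point modest.

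A reader might infer more, and the documents do not support it:

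- *That the three models use three different sets.* At most two arise for each outcome.
- *That the model sequence was built to display the effect of adjustment.* The article lists the models and gives no such purpose.
- *That families who leave items blank bias the result.* No rate or pattern of non-response is given. Covariates missing before the intervention starts would mainly cost precision and comparability.
- *That imputing outcomes alone recovers almost nothing.* The imputation variables are not described, and the several activity measures could inform one another.
- *That Aim 2 is damaged in the same way.* Factor tests on slightly different subsets are ordinary, and no comparison across them is planned.

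**Conclusion.** The concern holds in a limited form. The stated imputation excludes the covariates that the Aim 1 models need. Under default handling, Models 1 and 2 may therefore use different children, and the intention-to-treat description is not secured.

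Counted from the reported sample of about 500, a 10-20% loss costs about 0.01-0.02 SD in detectable difference at ICC 0.04 and about 0.015-0.03 SD at ICC 0. The worst cases, 0.422 and 0.301 SD, do not exceed the stated upper limit of 0.43 SD. These sizes rest on an assumed missing rate, on assumed alpha, power and ICC, and on no gain from covariates; 20% is an extreme. With no missing demographic items the sets coincide. No stated figure is contradicted and no bias is demonstrated. This is a worthwhile, inexpensive improvement and does not invalidate the primary analysis.

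**What to change.** In the Data analysis section, extend the planned imputation to the baseline activity variables, baseline height and weight, gender, race and parent education. For Aim 1, an acceptable alternative is to fill missing baseline covariates with a value computed without regard to arm and to add a missing indicator.

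Fit all three Aim 1 models to one common set of children, and say whether Model 3 keeps the Model 2 covariates. Keep the covariate-complete analysis as a sensitivity analysis, and report how many children lack each covariate, by arm. If the covariates were in fact complete or already imputed, saying so settles the point.

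The cost is a few sentences and a slightly larger imputation model, plus the assumption that covariates are missing at random given the other variables. No new data are needed.

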## Abstract

**Background:**

Physical inactivity is a recognized public health concern. Inadequate proportions of children in the U.S, including those of preschool age, are meeting physical activity recommendations. In response to low numbers of preschool children attaining appropriate physical activity levels, combined with the large number of young children who attend preschool, researchers have identified the need to devise interventions to increase physical activity at preschools. However, few multi-component interventions to increase physical activity in preschool children exist. The aims of this study were to observe the effects of a multi-component intervention on physical activity, sedentary behavior, and physical activity energy expenditure in 3-5 year-old children; identify factors that associate with change in those variables; and evaluate the process of implementing the multi-component intervention. The purpose of this manuscript is to describe the study design and intervention protocol.

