Although researchers have identified physical activity-promoting characteristics in preschools, there have been relatively few preschool physical activity intervention studies thus far [9,17], particularly randomized controlled trials [9,10]. Existing randomized controlled trials have shown ability to increase physical activity within the preschool setting [18-22]; however, these studies were conducted in different countries or specific cultural groups, were relatively short in duration, or were implemented primarily by well-trained interventionists and not children’s teachers. To address the low prevalence of meeting physical activity recommendations and lack of evidence regarding physical activity interventions in preschool children in the U.S., we designed the Study of Health and Activity in Preschool Environments (SHAPES) using known activity-promoting characteristics. SHAPES is a randomized trial designed to increase physical activity within preschool settings.

The aims of SHAPES were to (a) observe the effects of a multi-component intervention on physical activity, sedentary behavior, and physical activity energy expenditure in 3-5 year-old children; (b) identify factors that associate with change in physical activity, sedentary behavior, and physical activity energy expenditure during a school year in preschool children; and (c) evaluate the process of implementing a multi-component preschool intervention to increase physical activity and reduce sedentary behavior in 3-5 year-old children. SHAPES interventionists employed a flexible and adaptive approach to incorporating physical activity opportunities throughout the entire preschool day. Interventionists worked with teachers (e.g., workshops, on-site consultations) to develop and adapt their own daily activities to their specific classrooms. The goal was to maximize physical activity opportunities throughout the preschool day including outdoor play and classroom activities (e.g., center time, large group activities, pre-academic lessons). The purpose of this manuscript is to describe the SHAPES study design and intervention protocol.

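### Aim 2 asks which factors are associated with change in activity, but the only test stated for it is the group-by-factor interaction, which answers that question only in part

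*Protocol article*

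**What the plan says.** Four places in the protocol article bear on this point.

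- **The aim.** The Background section gives aim (b) as to "identify factors that associate with change in physical activity, sedentary behavior, and physical activity energy expenditure during a school year in preschool children". The Abstract has the same question in shorter form: "identify factors that associate with change in those variables". Neither mentions group or a differential intervention effect.
- **The candidate factors.** The Parent survey section says it collected demographic, home and "parental characteristics that were considered potential correlates of children’s physical activity". It does not call them moderators of the intervention.
- **The sample size.** For Aim 2 the Sample size section says that "calculations were based on a mixed-model regression approach, with condition (intervention versus control) as a fixed effect and preschool nested within condition" as the random effect. No interaction is mentioned. It then argues that the Aim 1 calculation is the more conservative one, the reason being: "Because more degrees of freedom were accounted for in this analysis".
- **The test.** The Data analysis section states: "For the second aim, a mixed-model ANCOVA was used, testing the interaction of group by factor". No other Aim 2 test is named.

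**The concern.** The aim is about association and the stated test is about effect modification. The interaction asks whether the relation between a factor and change differs between intervention and control. It does not ask whether the relation exists. A factor that predicts change strongly and equally in both groups is a correlate of change in the sense of the aim, yet it gives the interaction test nothing to find.

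If Aim 2 were reported from this test alone, such correlates would be missed. The article states a test that does not match its aim, so this is not a matter of detail left to an analysis plan. The Aim 1 analysis of the intervention effect is not affected.

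**Working it through.** **1. What the interaction measures.** Write the model as

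Y = b0 + b1·group + b2·factor + b3·group×factor + baseline + wave + preschool + error.

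Then b3 = slope(intervention) − slope(control). If the slopes are equal, b3 = 0 whatever their size. This is algebra and needs no assumed value.

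**2. The plan's own figure.** The article gives a detectable difference for Aim 1 only: 0.30 to 0.43 SD with 25 children per preschool and 8 preschools per group. Alpha, power and intraclass correlation (ICC) are not given. Assume two-sided alpha 0.05, power 0.80 and 14 degrees of freedom:

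(2.145 + 0.868) × sqrt(2 × (1 + 24 × ICC) / (25 × 8))

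- ICC 0: 3.013 × 0.100 = 0.301 SD
- ICC 0.043: 0.43 SD

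The stated range is plausible under these assumptions but cannot be confirmed without the variance components. The article states no detectable effect for Aim 2.

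**3. Illustration of the two tests.** Inputs from the article: 16 preschools × 25 children = 400, and about 500 children in total. Assumed: a factor split 50/50 within preschools (so the ICC drops out), an effect of 0.30 SD equal in both groups, residual SD 1, alpha 0.05.

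- Pooled association: 200 children per level. SE = sqrt(1/200 + 1/200) = sqrt(4/400) = 0.10 SD. Power = Phi(0.30/0.10 − 1.96) = Phi(1.04) = 0.85. Detectable at 80% power: 2.80 × 0.10 = 0.28 SD.
- Interaction: 100 children per group-by-level cell. SE = sqrt(4 × 1/100) = sqrt(16/400) = 0.20 SD. The true value is 0, so the rejection rate is alpha, 5%.

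**4. Detectable interaction on the same assumptions.**

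- 400 children: 2.80 × 0.20 = 0.56 SD
- 500 children: 2.80 × sqrt(16/500) = 2.80 × 0.179 = 0.50 SD

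Both exceed the Aim 1 range. Extra degrees of freedom lower the multiplier only from 3.01 to 2.80, while the interaction SE is twice that of the pooled association.

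**5. Simulation check.** 16 preschools × 31 children, assumed ICC 0.02, a continuous factor analysed within preschools, 2,000 runs per scenario. Slopes are in outcome SD per factor SD.

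| Slope in control / intervention | Pooled association rejects | Interaction rejects |
|---|---|---|
| 0.13 / 0.13 | 81% | 5.5% |
| 0.20 / 0.20 | 99% | 5.0% |
| 0.30 / 0.30 | 100% | 5.1% |
| 0 / 0.26 | 82% | 81% |
| −0.065 / 0.065 | 5.2% | 30% |

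Equal slopes are invisible to the interaction. For about 80% power it needs a slope difference of 0.26, twice the common slope of 0.13 that the pooled test needs. The last row shows the reverse: opposite slopes are found only by the interaction. The two tests answer different questions.

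**The case against.** The strongest reply is that the authors meant moderators. In a randomised trial that is a natural secondary question, and then the test is right and the aim is loosely worded. The Parent survey wording does not settle this, because it speaks of correlates of activity rather than of change and assigns the items to no test. The reply stands as a possibility. But the aim would then need rewording, and the Sample size statement would not hold for the interaction.

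A second reply is that a model with the interaction normally also contains the factor's main effect, and that the second and third Aim 1 models already include gender, race, parent education and length of the school day. This stands in part: nothing says those terms would go unreported. But the Data analysis section does not name them as Aim 2 tests, and most survey factors are not among them. With 0/1 group coding, the main-effect coefficient beside an interaction is the slope in the reference group only.

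The numbers also have limits. The 85% against 5% compares a false null with one that is true by construction, for a hypothetical factor. It does not carry over to school-level factors, where n is 16, and power would be lower for child factors that cluster by preschool.

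Three stronger readings are tempting but unsupported:

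- **That Aim 2 is not answered at all, or that a significant interaction would be a false correlate.** If the slopes differ, at least one is not zero, so the factor is associated with change in at least one group.
- **That the model forces one slope across all 16 preschools.** The article says only that preschool was random, never that the model has a random intercept alone, and a group-by-factor term already lets slopes differ by group.
- **That equal-slope factors would certainly be reported as null.** That is an inference about reporting which the text does not settle.

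**Conclusion.** The mismatch is real and should be resolved. The aim is worded as association in the Abstract and the Background section, and the Sample size section describes the Aim 2 model without an interaction. The only stated test is of effect modification, so it answers Aim 2 in part: it can find factors whose relation to change differs by group and has no power beyond alpha for factors that act equally in both.

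That a common slope gives a zero interaction rests on no assumption. It concerns the true interaction; the estimate varies around zero. The sizes (85% against 5%, and detectable effects of 0.28 SD for association against 0.56 SD for interaction at 400 children) rest on alpha 0.05, residual SD 1 and a balanced factor that varies within preschools. The 85% also assumes a 0.30 SD effect, and the detectable effects assume 80% power. The article does not show whether the aim or the test is misworded.

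**What to change.** Choose one of two routes.

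1. **Keep the aim.** For Aim 2, test each factor's association with follow-up activity, adjusted for baseline, group and wave, with preschool random and no interaction term. Report group-by-factor separately and label it exploratory effect modification.
2. **Keep the test.** Reword Aim 2 in the Abstract and Background as identifying factors that modify the intervention effect. Correct the Sample size statement that the Aim 1 calculation is conservative for Aim 2, and give the detectable interaction with its assumptions.

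The first route costs one sentence in the Data analysis section and one extra model per factor. The second costs only edits to the text. Neither needs new data.
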